**How will patients be contacted?**

We will request that participating clinicians schedule an appointment to discuss abnormal BMD results with the patient during an office visit. For patients with a scheduled appointment, we will approach the patient after they have been roomed for this appointment, prior to the discussion with their clinician. The study coordinator will inform patients about the study, will confirm eligibility, and obtain written informed consent in a private room. When there is insufficient time to consent a scheduled patient prior to the appointment time, the study coordinator or clinical assistant may contact the patient by phone and request the patient arrive 15 minutes early to the appointment.

**Recruitment Materials (if applicable):**

Clinicians will be contacted by e-mail to inform them of their patient's eligibility for the study and request permission for us to approach them.

**Patient Population:**

**Number (total, each subgroup)** 150, 50,50, and 50

We expect that 30 patients will take part at Olmsted Medical Center, Rochester

**Gender:**

Male:

Female: X

Ages: 50 to 90 years

**Clinician Population:**

Number (max. total): 100

Male: X

Female: X

Ages: > 21 years of age

**Inclusion Criteria:**

- 1. Peri/ post menopausal Caucasian, Black, Hispanic and Asian women aged 50-90 with a T-score < -1.0.
  2. Identified by their providers as potentially eligible for treatment with a bisphosphonate.
  3. Are available for phone follow-up 6 months after randomization.
  4. Patients with FRAX <20% risk who have taken a bisphosphonate for < 5 years.

**Exclusion Criteria:**

1) Patients with FRAX >20% risk who are taking bisphosphonates.

2) Have major learning barriers (in their provider's judgment), such as hearing impairment, or dementia, that would compromise their ability to give written informed consent

3) Are non-English speaking

**Step-by-Step Schedule (include all procedures, therapies – attach a table or flow chart if there are multiple procedures or visits and indicate the window of number of days in which the participant may return for follow-up visits):**

See attachment (Protocol Steps - Trial Flowsheet)

**Biospecimen (types, number, volume, processing, storage):** Not applicable

**Plan for Dose Modification if Toxicity occurs (if applicable):** Not applicable

**Statistical Considerations**

**Endpoints**

**Primary:** Medication start/stop, knowledge, and patient involvement will be the primary outcome measures. Medication start / stop will be assessed at meeting with clinician and at 6 months via self-report and pharmacy records.

**Secondary:** Decisional quality (i.e. knowledge, decisional conflict) will be assessed at baseline and at 6 months via phone surveys.

Normalization Process Analysis: At the end of the study, we will have results concerning the efficacy of the decision aid from the trial, as well as evidence of the extent to which nurses can facilitate the normalization of the decision aid into clinical practice.

Secondary analysis of videotaped patient clinician encounters. Two reviewers working independently and in duplicate will review the video recordings to determine eligibility and to extract data for analyses. Videotapes of eligible encounters will be reviewed to identify characteristics of patients, clinicians and patient-clinician interactions associated with use of the decision aid in clinical practice after the trial is complete.

**Power Statement:**

We plan to enroll and randomize 150 eligible patients. While this number of patients is insufficient to reach a definitive answer about the efficacy of our decision aid and its' effects on adherence, it is sufficient to ascertain meaningful differences in tool acceptability and knowledge gains as well as inform a plausible effect size in relation to its impact on adherence. Thus, we will be powered (80%) to detect a difference (alpha = 0.05) in adherence rates at 6 months of 30%. While a minimally important increase in adherence has not been reported, a 10% increase (e.g. from 65% to 75%) appears as the smallest difference that could justify the use of decision aids in practice. We will pool patients from the first pilot (with the exception of the low risk patients on bisphosphonates at time of recruitment), which will generate 95% confidence intervals with a precision of 17%, or a 90% confidence interval (akin to a one-sided hypothesis test) of 14% (44). This means that we have enough power to abandon plans for a multicenter trial when the point estimate of our trial indicates a decrease in adherence because of the use of the decision aid of greater than or equal to 7% or greater than or equal to 4% respectively.

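### The Power Statement presents a precision result as power: at its own half-widths, an aid with no effect would meet the abandonment criterion only about 21% (95% rule) or 32% (90% rule) of the time

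*Protocol*

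**What the plan says.** The Power Statement in the Protocol first uses power in its technical sense for 6-month adherence: "we will be powered (80%) to detect a difference (alpha = 0.05) in adherence rates at 6 months of 30" percentage points. It then sets the smallest worthwhile gain: "a 10% increase (e.g. from 65% to 75%) appears as the smallest difference that could justify the use of decision aids in practice".

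Next it describes the precision expected once patients from the first pilot are pooled in: "which will generate 95% confidence intervals with a precision of 17" points. A second figure is given for the one-sided view: "or a 90% confidence interval (akin to a one-sided hypothesis test) of 14" points. From these the section draws the conclusion at issue: "This means that we have enough power to abandon plans for a multicenter trial". The rest of that sentence makes the conclusion conditional on an estimate that shows adherence lowered by at least 7 points (95% interval) or 4 points (90% interval).

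No true effect and no probability are attached to this last claim. It is the only criterion in the Protocol for whether a multicentre trial should be dropped.

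**The concern.** A confidence interval half-width tells the reader what a given estimate would rule out if it were observed. Power tells the reader how likely such an estimate is when the truth takes a particular value. The Power Statement moves from the first to the second without any step in between. Because the same paragraph has just used the word with an 80% figure and an alpha level, a reader is likely to give it the same meaning here and to suppose that the pooled data would usually identify an aid not worth pursuing.

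What is at stake is how the criterion is understood. If it is seldom met even when the aid does nothing or does modest harm, then failing to meet it says little, and the plan should not leave the reader thinking otherwise.

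**Working it through.** **Inputs, all from the Power Statement.** Smallest worthwhile gain +10 points. Half-widths 17 points (95%) and 14 points (90%). Triggers: an estimate at or below -7 points (95%) or -4 points (90%).

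**Step 1: reproduce the plan's triggers.** The upper limit equals the estimate plus the half-width. Setting it equal to +10 gives:

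- 95%: 10 - 17 = -7
- 90%: 10 - 14 = -4

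Both match the plan exactly.

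**Step 2: standard errors implied by the half-widths.**

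- 95%: 17 / 1.960 = 8.67 points
- 90%: 14 / 1.645 = 8.51 points

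The two half-widths agree with each other within rounding: 8.67 × 1.645 = 14.27.

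**Step 3: chance of meeting the criterion.** For a true difference d, P = Φ((trigger - d) / SE). At d = 0:

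- 95%: Φ(-7 / 8.67) = Φ(-0.807) = 21.0%
- 90%: Φ(-4 / 8.51) = Φ(-0.470) = 31.9%

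| True difference (points) | 95% rule, trigger -7 | 90% rule, trigger -4 |
|---|---|---|
| +10 | 2.5% | 5.0% |
| +5 | 8.3% | 14.5% |
| 0 | 21.0% | 31.9% |
| -7 | 50.0% | 63.8% |
| -10 | 63.5% | 76.0% |
| -15 | 82.2% | 90.2% |

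**Step 4: true effect that gives an 80% chance.** d = trigger - 0.8416 × SE.

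- 95%: -7 - 0.8416 × 8.67 = -14.3 points
- 90%: -4 - 0.8416 × 8.51 = -11.2 points

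**Step 5: what not meeting the criterion tells the reader.** Under the 95% rule it happens with probability 100 - 21.0 = 79.0% at no effect and 100 - 2.5 = 97.5% at a true 10-point gain. Under the 90% rule the figures are 68.1% and 95.0%. It is the usual result in either case, so it separates the two poorly.

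**Step 6: precision needed for the claim to hold at no effect.** For an 80% chance of excluding +10 when d = 0, SE = 10 / (z + 0.8416).

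- 95%: 10 / 2.802 = 3.57 points, half-width 7.0, sample (8.67 / 3.57)² = 5.9 times the pooled one
- 90%: 10 / 2.487 = 4.02 points, half-width 6.6, sample (8.51 / 4.02)² = 4.5 times the pooled one

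**Sensitivity to rounding.** If the half-widths are off by up to 0.5 point and the triggers move with them, the zero-effect values run from 20.0% to 22.0% (95% rule) and from 30.5% to 33.5% (90% rule).

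**The case against.** The best defence is that the sentence is conditional. Read to its end, it says that if the estimate falls low enough, the data suffice to abandon. On that reading the content is right, the triggers are exact, and power is just a loose word for precision. The rule also does what it appears built to do: an aid with a true 10-point benefit would be abandoned only 2.5% or 5% of the time. All of this stands. It shows that no figure is wrong, but it does not supply the power claimed. A rule conditional on the estimate has no power to report.

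The same section also admits that 150 patients cannot settle the effect on adherence and that 80% power applies only to a 30-point difference. Adherence is not among the outcomes listed under Endpoints. These facts reduce the weight of the point. They do not cover the abandonment sentence, which is offered as something the pooled data can do despite that limit.

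Zero is one choice of true effect, and the plan names none. For that reason the working gives a range. The chance stays below 80% for both rules at every true effect from +10 down to a 10-point fall.

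A reader might infer that the sponsor would take a missed trigger as grounds to go ahead with the multicentre trial. The Protocol does not say so. The criterion runs in one direction only, and nothing defines a pass.

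**Conclusion.** The point holds as a misuse of the word power; it is not an arithmetic error. The triggers of -7 and -4 points are the correct boundaries for excluding a 10-point gain. The sentence nevertheless claims a property that the stated precision does not give. The chance of meeting the criterion is about 21% (95% rule) or 32% (90% rule) at no effect and 50% or 64% at a true 7-point fall. It reaches 80% only at a true fall of about 14 or 11 points.

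The 21% and 32% are the rule's power when the aid has no effect. They should not be read as error rates.

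The figures assume a normally distributed estimate and take the half-widths as stated. The half-widths cannot be checked in full because the number of pilot patients is not given. If they were revised, the triggers would have to move with them and the probabilities would need to be recalculated.

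Severity is minor: the rule, sample size, endpoints and analysis do not change, and the section already concedes that the adherence evidence will not be definitive.

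**What to change.** In the Power Statement, remove the claim of enough power and put a precision statement in its place, for example:

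*An observed fall in adherence of at least 7 (4) points would exclude a 10-point gain at the 95% (90%) level. Given the half-widths stated above, the chance of observing this is about 21% (32%) if the aid has no effect, and it reaches 80% only for a true fall of about 14 (11) points. Not meeting this criterion is therefore uninformative about whether the aid is worth pursuing.*

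If the half-widths are updated when the pilot numbers are confirmed, update the triggers and probabilities together. The cost is a rewording of one sentence and a less favourable description of the rule. No patients, visits or analyses are added.

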**Data Analysis:**

We will use hierarchical models (that take into account clustering/contamination) to estimate the absolute difference in bisphosphonates initiation and adherence rates between groups and the associated 95% confidence interval. We will use similar analyses for other dichotomous outcomes (e.g., adherence). We will use generalized estimation equations to compare the change in intermediate continuous outcomes (decisional conflict, knowledge) by arm after adjusting for clustering across physicians. With the exception of the low risk group on treatment, an analysis of Osteo II data may be combined with the Osteo I Choice study.

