**Methods**

**Description of Recruitment Methods:**

The Olmsted Medical Center (OMC), Rochester, has been added as a site. OMC study coordinators will recruit and consent patients. Enrolled patients and clinicians who consent to having the clinical visit recorded will be video and/or audio recorded via the FLIP cameras. Participating clinicians and patients will complete surveys following each encounter. The OMC study coordinator will notify the Mayo Clinic study coordinator each time a patient has enrolled in the study and arrange for all data (surveys, case report forms) and the FLIP camera to be hand delivered to the Mayo Clinic study coordinator.

In the event that there are any modifications in consent documents, the Mayo Clinic Study Coordinator will submit modifications to the OMC IRB, and provide revisions to the OMC Study Coordinator.

The coordinating center PI ([name]) has all contact information for OMC personnel, and will communicate / ensure that OMC has the most current version of the protocol and any amendments to the protocol.

Any deviations from the protocol by OMC will be communicated to the Mayo Clinic study coordinator or PI within 3 business days.

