When a patient has consented to participate in the study, the 3 identified nurses will meet with their patient and do the following:

After the patient has met with the study coordinator and provided informed consent to participate, the clinician will meet with their patient as they usually do in the examination room. If the clinician and their patient agree to do so, their visit will be videotaped. The consent document for clinician will have the following language:

“Your patient will be randomized to one of three groups by chance. Depending on which group your patient is in, you may share information about your patient’s treatment options, including bisphosphonate therapy, using different visual aids. If you and your patient agree to do so, your visit with your patient will be videotaped. If your patient is randomized to the control arm, you will meet with your patient in the usual fashion. If your patient is randomized to the FRAX or the FRAX + decision aid arm, you will discuss their fracture risk with them. Following your visit with your patient you will be asked to answer a short survey of 3-4 questions, which should take about one minute to complete.”

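### Knowledge and decisional conflict are analysed as change from a baseline never placed before or after the visit; if it follows the visit, the change measures retention, not effect

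*Protocol*

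**What the plan says.** - **Status of the outcome.** Endpoints: "Medication start/stop, knowledge, and patient involvement will be the primary outcome measures". Knowledge appears again in the same section as part of decisional quality, under the secondary endpoints.
- **Times.** Endpoints, on knowledge and decisional conflict: they "will be assessed at baseline and at 6 months via phone surveys". No other time is given for them, and baseline is not defined relative to the visit.
- **Analysis.** Data Analysis uses generalized estimating equations to "compare the change in intermediate continuous outcomes (decisional conflict, knowledge) by arm after adjusting for clustering across physicians". That sentence does not name the two ends of the change; baseline and 6 months are the only pair the protocol supplies.
- **Surveys timed against the visit.** Description of Recruitment Methods: "Participating clinicians and patients will complete surveys following each encounter". This is in the text on the added site. It neither calls that survey baseline nor lists its content.
- **Before the visit.** How will patients be contacted?: "we will approach the patient after they have been roomed for this appointment, prior to the discussion with their clinician". Eligibility and written consent follow, and no questionnaire is mentioned. The account of the visit has the same order: "After the patient has met with the study coordinator and provided informed consent to participate, the clinician will meet with their patient".
- **Schedule.** For the step-by-step procedures the protocol says "See attachment (Protocol Steps - Trial Flowsheet"). That attachment is not part of the text at hand.

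**The concern.** A change score shows a treatment effect only if its starting value was taken before treatment could act. Here the intervention is delivered within a single visit. The only patient survey that the text places relative to that visit comes after it, and the steps described before it are rooming, eligibility and consent. The time there is short: when consent cannot be fitted in, the patient may be asked to arrive 15 minutes early.

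If the first knowledge score is the post-visit one, the aid's immediate effect is already in the starting value and is subtracted out. An aid that works and whose effect lasts would show no difference. An aid that works and whose effect partly fades would appear worse than control.

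Knowledge is a primary outcome. The Power Statement concedes that 150 patients cannot settle adherence and rests the sample size partly on being able to show gains in knowledge, so the analysis of knowledge carries much of what this trial can deliver.

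**Working it through.** **The plan's own power figure.** The only power calculation is for adherence: 80% power, alpha 0.05, a difference of 30 percentage points at 6 months. With 50 per arm and a two-sided test it is met. The least favourable pair, 35% against 65%, needs 43 per arm (49 with continuity correction), and 50 per arm gives 86% power. This has no bearing on knowledge, for which no effect size, SD or correlation is stated.

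**Inputs**
- From the protocol: 50 per arm (Patient Population); alpha 0.05 (Power Statement), taken as two-sided.
- Assumed: immediate arm difference D = 0.6 SD in the direction of benefit; SD of 1 at each time; within-patient correlation rho of 0.3, 0.5 or 0.7; share r of the effect kept at 6 months; comparison of two arms; no clustering and no dropout.

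**Step 1: what the change estimates.** Randomisation makes the expected arm difference 0 before the visit. It is D just after the visit and rD at 6 months.
- Pre-visit baseline: rD - 0 = rD.
- Post-visit baseline: rD - D = (r-1)D.

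| r | Pre-visit baseline | Post-visit baseline |
|---|---|---|
| 1 | +0.60 SD | 0 |
| 0.75 | +0.45 SD | -0.15 SD |
| 0.5 | +0.30 SD | -0.30 SD |

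**Step 2: rejection rate with a post-visit baseline.** The SD of the change is sqrt(2(1-rho)), and the noncentrality is contrast / (SD × sqrt(2/50)) = 5 × contrast / SD. For rho = 0.5 the SD is sqrt(2 × 0.5) = 1. At r = 0.5 the noncentrality is 5 × (-0.30) = -1.5, and a t test rejects in about 32% of trials, against the aid.

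| r | rho 0.3 | rho 0.5 | rho 0.7 | Direction |
|---|---|---|---|---|
| 1 | 5% | 5% | 5% | error rate only |
| 0.75 | 9% | 11% | 16% | against the aid |
| 0.5 | 24% | 32% | 48% | against the aid |

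A direct comparison of post-visit scores, under the same assumptions, has noncentrality 5 × 0.6 = 3.0 and about 84% power.

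**Step 3: efficiency with a pre-visit baseline.** The change has variance 2(1-rho). Adjusting the 6-month score for the pre-visit score leaves variance 1 - rho². The ratio is (1 - rho²) / (2(1-rho)) = (1+rho)/2, which is below 1 for every rho below 1. At full retention, with contrast 0.6:

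| rho | SD, change | Power, change | SD, covariate | Power, covariate |
|---|---|---|---|---|
| 0.3 | 1.183 | 71% | 0.954 | 88% |
| 0.5 | 1.000 | 84% | 0.866 | 93% |
| 0.7 | 0.775 | 97% | 0.714 | 99% |

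**The case against.** The strongest reply is that nothing in the protocol calls the post-visit survey the baseline.
- Baseline ordinarily means before the intervention.
- A coordinator is with the patient before the clinician's discussion, so a pre-visit questionnaire is feasible.
- Speaking of gains in knowledge, as the Power Statement does, suits a starting point before the visit.
- The post-visit surveys are described in the added-site text as hand delivered, whereas Endpoints speaks of phone surveys, so they may be different instruments.
- The flowsheet, where survey timing belongs, is not shown.

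All of this stands. It rules out a stronger reading that a reader might infer: that the planned change score does subtract the aid's own effect. The documents support that only as one of two readings.

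A second tempting inference, that the analysis misses the effect on either reading, is also unsupported. With a pre-visit baseline, change is a valid randomised comparison with the right sign, and it estimates the effect still present at 6 months. Nor can one say that no immediate post-visit knowledge score is collected, since the content of the post-visit survey is not given.

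It might also be said that such detail belongs in the statistical analysis plan. When a survey is given is trial conduct, however, and the protocol itself chose change as the measure. What survives is an undefined starting point for a primary outcome, combined with a method that fails on one reading and is the less efficient choice on the other.

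**Conclusion.** The point holds as a conditional. The visible protocol does not fix whether the first knowledge and decisional conflict score comes before or after the visit, and the stated change analysis is sound only in the first case.

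- **Post-visit:** the contrast is (r-1)D. This is algebra and does not depend on the assumed effect size. The comparison then describes retention and is null or reversed whenever r is between 0 and 1.
- **Pre-visit:** the contrast is rD. The analysis is valid, and the cost of using change is lost power: 17 percentage points at correlation 0.3 (88 - 71), 9 at 0.5 (93 - 84) and 2 at 0.7 (99 - 97), for D = 0.6 SD and full retention.

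The percentages are illustrations, because the protocol gives no effect size, SD, correlation or retention for knowledge, and they ignore clustering and dropout. The point deserves correction rather than a note because knowledge is a primary outcome and one change of wording improves the analysis on both readings.

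**What to change.** 1. In Endpoints, say for each survey whether it is taken before the visit, directly after it or at 6 months, by what mode, and whether it contains the knowledge and decisional conflict items. Make Description of Recruitment Methods, Data Analysis and the flowsheet agree with it.
2. In Data Analysis, replace the comparison of change. Compare arms with GEE, allowing for clustering by clinician, on the 6-month score and, separately, on the post-visit score where it is collected.
3. If a pre-visit score is collected, enter it as a covariate. Never subtract a post-visit score from a later one.

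**Cost:** wording only. The 6-month score is planned on either reading and any other score is used only if already collected, so no new assessment is needed. The GEE framework and the adjustment for clustering stay as they are.

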**Human Safety Aspects**

**Risks**: This is a minimal risk protocol.

**Individual Patient Stopping Rules** (if applicable):

**DSMB** (if applicable):

Members: Not applicable

Charter:Not applicable

**Stopping Rules for Efficacy and** Safety (if applicable): Not applicable

**Questionnaires that ask about Depression** (if applicable)

Included in study? Yes  No

If “Yes”, state the plan of management for subjects with possible depression:

When submitting this form to IRBe, attach a copy of the budget and consent form. Thank you.
